### Data monitoring and ethical approval

This study is being monitored by a steering committee. To verify the data, the study coordinator, a member of the steering committee, will visit the participating centers frequently. All patient data collected during the study will be analyzed and documented according to Good Clinical Practice.

Ethical approval has been obtained from the Ethics Committees at Erasmus Medical Center, Sint Franciscus Gasthuis, Maasstad Hospital, Vlietland Hospital, Albert Schweitzer Hospital, The Oosterschelde Hospital, Hospital Walcheren, and ZorgSaam Hospital.

## Statistics

### Sample size

Sample-size calculations were based on the AUC HAQ using primary data from the BeST study[15], where the mean AUC HAQ of the combination therapy was 7.7 (SD 5.5) and the mean AUC HAQ of monotherapy was 10.5 (SD 7.4)

To detect this difference using a significance level of α = 0.05 and a power of 80%, ninety patients are needed in each treatment arm. This number of patients is sufficient to detect a difference of 6.1 AUC DAS and 20% of patients with or without radiographic progression towards baseline (α = 0.05; power 80%).

In total, 810 patients will be needed. Allowing for a participation rate of 80%, 1012 patients will have to be screened, which corresponds with 337 patients in each probability group. With seven hospitals involved, we expect to recruit 34 eligible patients a month.

### Analysis

Baseline characteristics will be presented with descriptive statistics. Number, mean, standard deviation, and minimum and maximum values will be used for continuous data; and absolute and relative frequencies will be used for categorical data.

Data on the primary outcomes HAQ and DAS will be analyzed per strata of probability (HP, IP and LP) over time using the AUC (area under the curve), which is an appropriate method for detecting therapy difference early in the follow-up period. Analysis will be performed using intention-to-treat analysis and per-protocol analysis. Data on radiological progression will be analyzed using the non-parametric Mann-Whitney U test. All data will be analyzed using STATA 9.0 and R.

### Cost-effectiveness analysis

In the study, direct and indirect costs will all be considered within the one-year period following randomization. Direct medical costs will be calculated on the basis of use of resources within the healthcare sector. Indirect costs are defined as the cost of production lost through illness or its treatment.

Medication use will be recorded on the basis of the trial medication prescribed and will be valued on the basis of national cost prices excluding value added tax (VAT) and markups for the acquisition and administration of medication. The use of over-the-counter medication will be recorded through patient questionnaires. The cost of over-the-counter medications will be calculated on the basis of retail prices.

Adverse events and serious adverse events will be recorded during the trial period. To estimate the average cost per type of adverse event, scenario studies will be conducted.

Data on medical care utilization outside the hospital and on absence from work will be collected using a patient questionnaire that includes questions on healthcare visits, medication, quality of life, and number of working days lost due to joint complaints or other disorders. As a basis for establishing the level of production losses, we will use the average income per person by age and gender for 2008–2010.

Cost data will be analyzed per probability stratum by comparing the three treatment groups in each stratum. Incremental cost-effectiveness ratios will be calculated by dividing the difference between the costs of the treatment strategies by the difference in the DAS and HAQ. At baseline, 6 months and 12 months, the effects of arthritis and therapy on utility will be measured using the EQ5d.

## Discussion

The overall objective of this study is to determine the most effective induction therapy for patients with early arthritis who are at risk of persistent arthritis. An important difference between this study and previous studies is that we are able to start treatment before patients have fulfilled the ACR criteria. To do so, we are being guided by the prediction model of Visser for early arthritis, which is used to stratify patients according to a low, intermediate or high risk of persistent arthritis. The induction therapies we use reflect current rheumatology practice, ranging from NSAIDs in the low probability group to combination DMARD therapy in the high probability group.

This study has two specific objectives focused on induction therapy in the HP group. The first is to establish whether MTX-monotherapy is as effective as combination DMARD therapy (MTX-SSZ-HCQ) in patients who are at a high risk of persistent arthritis. For although established RA combination therapy have been shown to perform better than monotherapy in terms of reducing disease activity and radiological progression [10-15,17,19,20], there is no evidence in early arthritis that monotherapy MTX is as effective as combination DMARD therapy, despite its accepted use in daily clinical practice. Moreover all these studies analyzing the combination of DMARDs show that their effectiveness may have been modified by corticosteroids.

Therefore the second specific objective concerns the use of corticosteroids. In daily practice corticosteroids are widely used as bridging therapy since the maximum therapeutic effect of DMARD will take at least three months. But until now, it is unclear what the starting dosage should be and for how long corticosteroids should be prescribed. We intend to establish whether one intramuscular bolus of prednisolone is as effective as the cumulative high dose over three months of oral prednisolone.

Our choice of treatment in the intermediate group was based on the 50% chance that people in this group have a self-limiting disease, which makes overtreatment an important issue. To be able to choose the optimal benefit-harm ratio for these patients, we decided to include various treatment intensities, MTX being the most intensive. We expect single DMARD therapy to be safe, and that overtreatment will probably be less harmful than the risk of irreversible joint damage [39]. Furthermore, if any of these patients goes into remission, their medication will also be tapered off quickly.

Mild treatment options were chosen for patients in the low probability group, hardly any of whom are expected to progress to persistent arthritis.

The trial is being conducted in the southwestern Netherlands, and has been received with great enthusiasm by the participating centers, particularly because rheumatologists there feel that it will answer very practical questions. Because treatment choices have been made by consensus between all participating rheumatologists, it is likely that the results of the trial will be implemented easily in daily practice.

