The main aim of the present study is to determine which prediction-guided treatment strategy is superior in patients with recent-onset arthritis who, on the basis of the Visser Prediction rule, are stratified as having a low, intermediate or high risk of developing persistent arthritis.

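### The two specific high-probability objectives ask whether one strategy is as effective as another, but the aim, sample size and stated purpose of the analysis are for detecting a difference and no margin is given

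*Protocol article*

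**What the plan says.** The last paragraph of the Background sets a superiority aim: "The main aim of the present study is to determine which prediction-guided treatment strategy is superior". The Discussion opens in the same direction: "The overall objective of this study is to determine the most effective induction therapy for patients with early arthritis".

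The Sample size section plans on a difference. It takes AUC HAQ figures from an earlier trial, in which "the mean AUC HAQ of the combination therapy was 7.7 (SD 5.5") and the monotherapy mean was 10.5 (SD 7.4). It then sets the number of patients with the words "To detect this difference using a significance level of α = 0.05 and a power of 80"%, and arrives at 90 per arm. The Analysis section justifies the AUC as suited to finding treatment differences early in follow-up. It plans both intention-to-treat and per-protocol analyses.

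The Discussion then gives the high-probability stratum two specific objectives in a different form. One is "The first is to establish whether MTX-monotherapy is as effective as combination DMARD therapy (MTX-SSZ-HCQ"). The other is "We intend to establish whether one intramuscular bolus of prednisolone is as effective as the cumulative high dose over three months of oral prednisolone". The article states no margin, one-sided level or confidence-interval rule for either.

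**The concern.** A question about equal effectiveness and a question about a difference need different evidence. The first needs a confidence interval that excludes a deficit fixed in advance as too large. The second needs an interval that excludes zero. A trial planned for the second can end with an interval that includes zero and also includes a large deficit, and that result answers neither question.

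These are the only objectives the article labels as specific. The Abstract says that rheumatologists already prefer to start with methotrexate monotherapy and bridging corticosteroids, and the Discussion expects the results to be taken up easily in practice. With the objectives worded as they are, a reader of the final report could take a null comparison as support for the less intensive strategy when the data had not excluded a meaningful loss.

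**Working it through.** **Inputs.** From Sample size: means 7.7 and 10.5, so a difference of 10.5 − 7.7 = 2.8; SDs 5.5 and 7.4; α = 0.05; power 80%; 90 per arm. The article does not state sidedness, so two-sided is assumed. Normal approximation throughout, with no adjustment for multiple comparisons.

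**1. Reproducing 90 per arm.** n = (1.96 + 0.842)² × (5.5² + 7.4²) / 2.8² = 7.85 × 85.01 / 7.84 = 85.1, so 86 per arm (87 with the t distribution). Power at 90 is about 82%. A one-sided 0.05 test would need 68, which does not fit. The stated figure is a slightly conservative two-sided difference calculation.

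**2. Precision at 90 per arm.** SE = √(85.01 / 90) = 0.972. The 95% half-width is 1.96 × 0.972 = 1.90. An observed deficit just under 1.90 is non-significant, and its upper confidence limit is about 1.90 + 1.90 = 3.8, beyond the planned 2.8.

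**3. How often a real deficit gives a non-significant result.** Probability ≈ Φ(1.96 − deficit / 0.972).

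| True deficit (AUC HAQ) | Non-significant |
|---|---|
| 1.4 (half of 2.8) | 70% |
| 2.0 | 46% |
| 2.8 | 18% |

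**4. What the same sample could do with a margin.** Non-inferiority power with a true difference of zero and one-sided 0.025 is Φ(margin / 0.972 − 1.96). The article gives no margin, so these are assumed values.

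| Margin | Power at 90 per arm | Needed per arm for 80% |
|---|---|---|
| 2.8 (whole planned benefit) | 82% | 86 |
| 2.64 | 78% | 96 |
| 2.1 | 58% | 152 |
| 1.4 | 30% | 341 |

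The 2.64 row is the minimal clinically important HAQ difference in Data collection, 0.22, multiplied by 12. This assumes that the AUC is in HAQ-months over one year, and the article does not state the units or the window.

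**5. The corticosteroid contrast.** Both arms receive combination therapy, and the article gives no planning effect or SD for this comparison. With a common SD of 5.5 to 7.4, power at a margin of 2.8 runs from 93% down to 72%, and at 1.4 from 40% down to 25%.

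**The case against.** The superiority reading is dominant. The Abstract, the main aim, the overall objective and the sample size all point that way, and the equal-effectiveness wording appears only in the Discussion. To establish whether something is so is also an open question, not a claim. For the first objective the surrounding text challenges the accepted use of monotherapy, and a finding that combination therapy is better would answer it with about 82% power. This stands. It makes loose wording a plausible explanation, and it favours rewording over redesign. It fits the second objective less well, because no expected difference between the corticosteroid regimens is stated.

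A reader might go further and infer that the plan will treat a non-significant test as proof of equivalence, or that this is its only route to the claim. The article does not support that. It states no such decision rule and names no test for AUC HAQ or AUC DAS, and a fuller document could contain a margin. A margin stated elsewhere would still not change the basis on which 90 per arm was calculated. The planned per-protocol analysis would suit a non-inferiority comparison but does not create one.

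**Conclusion.** The mismatch is within the article and it holds. The two specific objectives are worded for equal effectiveness, while the aim, the sample size and the stated purpose of the AUC analysis are for a difference. With 90 per arm, a non-significant AUC HAQ result can leave open a deficit of about 3.8, and a true deficit of 1.4 goes undetected in 70% of trials. Non-significance therefore cannot answer either objective as worded. These figures assume that the planning SDs apply in the high-probability stratum, that 90 per arm are analysed and that the test is two-sided.

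It is also tempting to conclude that a margin of 2.64 would rescue the claim at almost no cost, since power would be 78%. The article does not support prescribing that margin:

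- It is 2.64 / 2.8 = 94% of the benefit assumed for combination therapy.
- If half that benefit were truly lost, the rule would still declare equal effectiveness in Φ((2.64 − 1.4) / 0.972 − 1.96) ≈ 25% of trials.
- It depends on an assumed time scale.
- Nothing in the article ties it to the intramuscular versus oral comparison.

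**What to change.** Reword both objectives in the Discussion as two-sided difference questions, in line with the Background aim and the Sample size section: whether AUC HAQ differs between methotrexate and combination therapy, each with high-dose corticosteroids, and between the intramuscular and high-dose corticosteroid regimens on combination therapy. Add that a non-significant result is inconclusive and will be reported with its 95% confidence interval, not as equivalence. This leaves the design and the number of patients unchanged. The cost is that the trial gives up the equal-effectiveness claim.

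If the sponsor wants to keep that claim, then before unblinding it must, for each of the two contrasts:

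- justify a margin;
- state the confidence-interval rule;
- require the intention-to-treat and per-protocol results to agree;
- report the power at 90 per arm for the margin chosen (from the table above where the planning SDs apply, and with its own SD assumption for the corticosteroid contrast).

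This route also needs no extra patients if that power is accepted. However, it is a substantive amendment to a trial already recruiting, and power falls to about 30% if the margin is half the planned benefit.
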